## Abstract

**Background:**

As the snacking pattern of European adolescents is of great concern, effective interventions are necessary. Till now health promotion efforts in children and adolescents have had only limited success in changing adolescents’ eating patterns and anthropometrics. Therefore, the present study proposes an innovative approach to influence dietary behaviors in youth based on new insights on effective behavior change strategies and attractive intervention channels to engage adolescents. This article describes the rationale, the development, and evaluation design of the ‘Snack Track School’ app. The aim of the app is to improve the snacking patterns of Flemish 14- to 16-year olds.

**Methods:**

The development of the app was informed by the systematic, stepwise, iterative, and collaborative principles of the Intervention Mapping protocol. A four week mHealth intervention was developed based on the dual-system model with behavioral change strategies targeting both the reflective (i.e., active learning, advance organizers, mere exposure, goal-setting, monitoring, and feedback) and automatic processes (i.e., rewards and positive reinforcement). This intervention will be evaluated via a controlled pre-post design in Flemish schools among 1400 adolescents.

**Discussion:**

When this intervention including strategies focused on both the reflective and automatic pathway proves to be effective, it will offer a new scientifically-based vision, guidelines and practical tools for public health and health promotion (i.e., incorporation of learning theories in intervention programs).

**Trial registration:**

NCT02622165 registrated November 15, 2015 on clinicaltrials.gov.

## Background

The dietary pattern of European adolescents with a high intake of energy-dense low-nutritious foods and a low intake of essential food groups is of great concern [1, 2]. In Flanders, 27 % of adolescents consume sweet snacks on a daily basis, and snacks between meals account for 20–24 % of their total energy intake [3, 4]. A recent study among Flemish 14- to 16-year-olds indicated a higher intake of unhealthy –fat- and/or sugar-rich– snacks (214.4 ± 147.3 g) than healthy snacks (122.0 ± 133.4 g) [5]. Given the association between unhealthy snacking and the development of obesity, dental carries and other chronic diseases during adolescence and later in life [6–8], attention to healthy snacking in adolescents is key.

Based on the bio-psycho-social model [9], the development of an effective health promotion intervention requires a multidisciplinary approach addressing multiple contexts both at the individual and environmental level. Most health promotion efforts to improve dietary behaviors in youth have focused mostly on schoolchildren and their families in enhancing knowledge and changing well-known environmental factors in order to improve dietary behaviors [10, 11]. However, till now these school- and family-based multicomponent interventions have had only limited success in changing adolescents’ eating patterns and anthropometrics [12–14]. Therefore, new approaches to influence dietary behaviors in youth should be considered based on new insights on effective behavior change strategies and attractive intervention channels to engage adolescents.

Michie and colleagues [15] conducted a meta-regression to identify the most effective techniques derived from different behavioral change theories on healthy eating and physical activity interventions and found that interventions combining self-monitoring with at least one other technique derived from the Control Theory (i.e., goal setting, feedback, review goals) of Carver and Scheier [16] were more effective than other interventions. In addition, an innovative in-depth analysis of theoretical explanations for behavior change following interventions (i.e., a comparison between the theoretical basis of an intervention, the delivery in practice = dose delivered, and the intervention receipt = dose received/exposure in participants) by the same authors [17] indicated a clear theoretical difference between intervention delivery and receipt. Participants reported a lower exposure than the dose delivered for all used theoretical methods apart from those based on operant theory. This latter result highlights the important role of operant techniques (i.e., rewarding/positive reinforcement) in behavior change.

Next, also personality theories provide important insight as they focus on differences between individuals. An important gap in intervention research is the effectiveness of interventions that take into account individual differences in personality to promote healthy diets [14]. This is unfortunate as unhealthy eating behaviors, such as the intake of energy dense snacks, are often driven by hedonic motives like eating for the palatability or the reward value of food in the absence of hunger rather than by homeostatic hunger or eating out of biological needs [18, 19]. Reward Sensitivity (RS) is a bio-psychological concept which reflects one’s ability to experience pleasure or rewarding feelings when exposed to positive (appetitive/palatable) stimuli [20] and has been found to play a critical role in eating unhealthy food products, overeating and becoming overweight or obese [5, 21, 22]. During adolescence, RS has an increased influence on behavior as the reward processing peaks while regulative control matures at a slower pace [23]. Taking into account RS in preventive health promotion among adolescents by using reward-based strategies might increase intervention effects in this population. However, little is known about the specific role of RS in food cue reactivity and learning processes to adopt healthy food preferences and healthy nutrition behavior. Therefore, the REWARD-project aimed to develop a new approach to motivate adolescents to opt for healthy snack choices by using reward-based learning and taking into account individual differences in RS.

Although recent insight on the role of learning theories in behavior change has increased considerably, we have to take care not to rely too much on a simplistic perspective. Kremers and colleagues [11] indicated that nutrition behaviors are the result of a joint function between conscious and unconscious processes. Dual-system models or dual-process models explain health behaviors as two interconnected mental systems, each operating according to different principles [24, 25]: a top-down reflective system including elaboration and cognitive efforts to build beliefs and decisions and a bottom-up impulsive/automatic system (i.e., habits) in which certain stimuli or cues are linked to certain behaviors based on earlier learned associations [11, 26]. Based on previous research and theoretical evidence [11, 24–26], it was decided to incorporate behavioral change methods and strategies in the intervention to influence the reflective pathway in addition to the reward-strategies that target the more automatic pathway. This broad framework is attractive as it allows to include other models that focus on unique determinants like personality theory and operant learning models that fit well with the bottom-up perspective as well as the Control theory that focuses more on the reflective pathway.

Finally, besides using new theoretical approaches, it is also warranted to revise the intervention channel to reach adolescents. Traditional channels, via school, family, and/or community, had only limited success in previous studies [12–14]. We therefore assume that intervention approaches imbedded in the actual world of adolescents are needed. Smartphones have a great potential to reach large numbers of adolescents as they have become an integral part of adolescents’ daily life and usage rates are rising significantly in European adolescents [27]. Recent systematic reviews have shown that mHealth interventions are promising in changing health behaviors in youth [28–30]. Additional advantages are the cost-effectiveness of the dissemination, lowered participant burden, flexible program tailoring, data for self-monitoring, and more visually appealing and engaging multimedia modalities [31]. Therefore, it was decided to deliver the intervention as an mHealth intervention.

This paper describes the rationale, design and methods of a four-week controlled trial designed to measure the effectiveness of an mHealth intervention named the ‘Snack Track School’ to improve adolescents’ snacking behavior. The first hypothesis is that the intervention will increase the healthy snack intake and reduce the unhealthy snack consumption (i.e., measured by a healthy snack index) of adolescents compared to the control group. Secondary hypotheses are that the intervention will 1) decrease the age- and gender-adjusted Body Mass Index, 2) positively influence socio-cognitive factors and habits related to healthy snacking, and 3) affect high reward-sensitive adolescents’ snacking behavior more than low reward-sensitive adolescents.

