#### Intervention components

The ‘Snack Track School’ app is a four week intervention and  constitutes of a virtual high school environment with typical school locations (i.e., classrooms, gym hall, bike area, bathrooms, etcetera) in which all participants have their own locker, their own Snack Track Tool, and their own ‘anonymous’ avatar, which they can customize as preferred based on several options (i.e., many options for head of character, clothes, shoes, gadgets). During the four-week intervention, every week of snack monitoring has its own story line and challenges.

The central idea of the ‘Snack Track School’ intervention is that participants earn credits/points based on the nutritional value of the snacks they consume (i.e., *positive reinforcement/providing rewards to influence automatic behavior*). For every snack the adolescents enter in the app via the ‘Snack Track’ tool, they will be awarded by points. The healthier the snacks they consume, the more points they will receive. These credits will be responsible for the progress in the weekly challenges of the four-week app. No negative points will be provided for unhealthy snacks as punishment can have contra-productive effects [38]. A large snack database was constructed based on the Internubel Trade Name database [39]. Points will be awarded according to the UK Ofcom Nutrient Profile model [40].

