### Data collection and outcome measurements

#### Primary outcome measure

The primary outcome consists of the *Healthy Snacking Index*. A Food Frequency Questionnaire (FFQ) was developed to measure average snack consumption in adolescents via 28 snack items. This new FFQ is based on an earlier FFQ instrument for children developed by Huybrechts and colleagues [51], but includes portion sizes that match adolescents’ intake patterns. Adolescents will indicate their answer in a list of six frequency categories, namely never or seldom; 1–3 days/month; 1 day/week; 2–4 days/week; 5–6 days/week; every day [51]. The FFQ contains four to six daily portion size categories per snack item and a list of common standard measures as examples. Snacks are in this study defined as all food items consumed outside (>30 min) of breakfast, lunch and dinner, in accordance to Rodriguez and Moreno’s definition of snacking [52]. The 28 snack items assessed in the FFQ are: dried fruit, fruit, raw vegetables, nuts and seeds, chocolate and pralines, candy bars, candy, dry cookies, other cookies such as chocolate cookies, breakfast rolls, pastries, breakfast cereals, unsweetened yoghurt, sweetened yoghurt, pudding, mousses, ice-cream, popsicles, sandwiches with sweet or savoury spread, cheese or meat cubes, chips and similar products, other savoury snacks such as bread sticks, sausage/cheese rolls and pizza, other fried snacks such as spring rolls and cheese croquettes, fries, kebab, hamburgers and pasta cups.

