The classification of snacks and drinks into healthy and unhealthy was based on the nutrient profiling model as developed by the UK NP Ofcom model [40]. This model calculates for each food product a score that represents its healthiness In order to apply this model, an average nutrient composition per FFQ category was needed to apply this nutrient profile model. The average nutrient composition per FFQ category was calculated by averaging the nutritional composition (obtained from the Belgian food composition table [39] expressed per 100 g) of the most frequently consumed food items by adolescents within that category, as reported in the HELENA study [53]. The average energy, sugar, and fat and sodium intakes per FFQ category were then calculated by multiplying the amounts (g) of the food consumed and the average nutritional values expressed per g (the average values per 100 g divided by 100) [39]. According to the average amount of sodium, sugar, fat and kJoules, fibre, proteins and the portion of fruit and vegetables or nuts present in the product the NP model gives the food product a score, if a food product scores more than 4 points it was considered unhealthy. The FFQ items crisps, other salty snacks, sausage/cheese rolls and pizza, other fried snacks, fries, hamburgers, cheese or meat cubes, icecream, popsicles, breakfast cereals, pudding, sandwiches with sweet or savory spread, mousses, chocolate, candy bars, candy, dry cookies, other cookies, breakfast rolls and pastries were considered to be unhealthy.

The daily intake of each FFQ category will be obtained by multiplying the frequency of consumption with the quantity of consumption per week (g) divided by 7. These daily intakes, will then be summed to obtain the daily intake of healthy snacks (g), and unhealthy snacks (g). Finally a health index for snacks will be calculated: (gram healthy snacks/‘gram healthy snacks + gram unhealthy snacks))*100. The reliability and validity of this FFQ to assess the healthy snack ratio for interventions purposes were tested and reported elsewhere [[name] unpublished]. The healthy snack index’ reliability was good and the validity was acceptable.

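### Hypothesis 1 claims both more healthy and less unhealthy snacking, but the single ratio index that measures it cannot show which of the two changed

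*Protocol article*

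**What the plan says.** The protocol article, Background, states as first hypothesis that the intervention "will increase the healthy snack intake and reduce the unhealthy snack consumption (i.e., measured by a healthy snack index"), compared with control. Under Primary outcome measure, the Healthy Snacking Index is the primary outcome. FFQ intakes are "summed to obtain the daily intake of healthy snacks (g), and unhealthy snacks (g"), and the index is then calculated from those totals as ("gram healthy snacks/‘gram healthy snacks + gram unhealthy snacks))*100". Study population and recruitment bases the sample size on this index alone.

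The listed secondary outcomes are anthropometry and cognitive variables. Total energy intake appears only among the explorative measures (Table 1). Data management and analysis applies linear mixed models to the primary and secondary outcomes. The two gram totals are therefore derived as a step towards the index but are not listed as primary or secondary outcomes.

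The Background itself describes the problem in separate gram amounts: more unhealthy "snacks (214.4 ± 147.3 g) than healthy snacks (122.0 ± 133.4 g").

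**The concern.** A hypothesis that one quantity rises and another falls needs evidence on each. The index is a function of the ratio of healthy to unhealthy grams and of nothing else. It rises if fruit or yoghurt is added on top of an unchanged intake of sweets and crisps. It also rises if both intakes fall, provided the unhealthy one falls further. If the primary test is significant and hypothesis 1 is reported as confirmed in the words used, a reader will conclude that unhealthy snacking went down when it may have been unchanged or higher. Snack energy could then have risen, which would run against the trial's own secondary hypothesis on body mass index.

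**Working it through.** **Inputs.** Healthy intake H = 122.0 g (SD 133.4) and unhealthy intake U = 214.4 g (SD 147.3), from Background. Index mean 37.8, SD 20.2; ICC 0.02 (school) and 0.03 (class); 3 schools × 12 classes × 15 pupils per arm; 20 % difference; 5 % significance; 80 % power; 33 % oversampling, all from Study population and recruitment.

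**The planned effect.** Read 20 % as relative: 0.20 × 37.8 = 7.56 points, so the target is 45.36. Two-sided n per arm = 2 × [20.2 × (1.960 + 0.842) / 7.56]² = 112.1. Design effect = 1 + 14 × 0.03 + 15 × 11 × 0.02 = 4.72. Product: 529 per arm, or 2.94 schools of 180, hence 3 schools and 540 pupils. 1080 × 1.33 = 1436.4, hence 1437. The plan's figures reproduce. An absolute difference of 20 points would need only 76 per arm, so the relative reading is the right one.

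**What the target requires.** An index of 45.36 means H/U = 45.36/54.64 = 0.830. An index of 37.8 means H/U = 37.8/62.2 = 0.608. The ratio must rise by 37 %, however that comes about. On the Background means (ratio-of-means index 36.3):

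| Unhealthy g/day | Healthy g/day needed | Change in healthy | Change in total snack weight |
|---|---|---|---|
| 214.4 (unchanged) | 0.830 × 214.4 = 178.0 | +56.0 | +17 % |
| 235.8 (+10 %) | 195.8 | +73.8 | +28 % |
| 147.0 (−31 %) | 122.0 | 0 | −20 % |
| 132.3 (−38 %) | 109.8 | −12.2 (−10 %) | −28 % |

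Totals are relative to 336.4 g; for the last two rows, 269.0/336.4 and 242.1/336.4.

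**Sensitivity to the starting point.** The Background means give 36.3, not 37.8. Splitting the total of 336.4 g to match 37.8 gives H = 127.2 g and U = 209.2 g. The rise needed is then 173.7 − 127.2 = 46.5 g with U unchanged, and 191.1 − 127.2 = 63.9 g with U up 10 %.

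**Sensitivity to averaging.** The mean of individual indices is not the index of the means. Individuals were simulated with the Background means and SDs, assuming H and U independent and gamma or lognormal (simulated mean index 34.0 and 35.0). A 20 % relative rise in the mean index needed about +27 to +31 g of healthy snacks per person with U unchanged, and +35 to +42 g with U up 10 %, if everyone adds the same amount. If each person's healthy intake is multiplied instead, the factors are 1.44 to 1.50 and 1.59 to 1.65, or mean rises of 54 to 60 g and 72 to 79 g.

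**Power for unhealthy grams.** The documents give no ICCs for gram outcomes. Borrowing those of the index, a 20 % fall is 42.9 g. SE = 147.3 × √(2 × DE / 540). With a design effect of 4.72, SE = 19.5 and power is 60 % (normal) or 39 % (t, 4 df for six schools). With a more conservative 5.0, SE = 20.0 and power is 57 % or 37 %. Any gain from baseline adjustment is ignored.

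**The case against.** The best defence is that the index is how the article chooses to define the hypothesis operationally, that the abstract's aim is only to improve snacking patterns, and that component analyses are commonly left to an analysis plan, which is not shown. Body mass index is tested separately and total energy intake is measured, so a rise in energy need not go unseen. Part of this stands: the article nowhere says that it will infer a fall in unhealthy grams from the index alone, and the omission of supplementary analyses is not itself the fault. What does not stand is the equation of a two-part statement with a ratio. That is in the article's own text, and no analysis detail can make a ratio test both parts.

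Three stronger readings are tempting and are not supported.

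- A reader might infer that the app will probably push the error in one direction, since every logged snack earns points and "No negative points will be provided for unhealthy snacks". The same section also stops credit after ten snacks and gives bonuses for six or fewer snacks and for at least two-thirds healthy. The sizes of those bonuses are not stated, so it cannot be shown that adding healthy snacks earns more than dropping unhealthy ones. Nor do the bonuses exclude it: going from two healthy and two unhealthy snacks to four and two keeps the first bonus and gains the second. Addition without reduction is plausible, not demonstrably likely.
- A reader might infer that non-snackers, whom the app rewards, will have an undefined index. The app bonus is per day, whereas 0/0 needs zero reported intake on all 28 FFQ items. The documents give no frequency for that.
- A reader might take any one gram figure above as the plan's implication. The amounts vary about twofold with the basis chosen; only the direction is firm.

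**Conclusion.** The concern holds as a mismatch between hypothesis 1 and its measure. The test of the index is valid and its sample size reproduces, but a significant result supports only a higher healthy share of snack weight. Either half of the hypothesis can fail while the primary test succeeds. That conclusion follows from the formula and needs no assumption. The amounts do: they rest on reading 20 % as relative, on the Background means standing in for the trial population, and, for the simulated figures, on assumed distributions with independent intakes. With unhealthy intake unchanged, the planned effect needs between about 27 and 60 g/day more healthy snacks across all bases. With unhealthy intake 10 % higher, it needs between about 35 and 79 g/day. The point should be corrected before results are reported; it does not undermine the design.

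**What to change.** Keep the index as the primary outcome, with its sample size. Then do one of the following.

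1. Restate hypothesis 1 as a higher healthy share of snack weight. This costs nothing and matches what the index measures.
2. Keep the two-part hypothesis and name daily healthy grams and daily unhealthy grams as outcomes, analysed with the same mixed model. Claim that healthy intake rose and unhealthy intake fell only if the index and both gram contrasts are each significant in the stated direction. Otherwise claim only a higher healthy share, if the index supports it. Because all three must succeed, no alpha adjustment is needed.

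The second option adds two models on variables that are already derived. Its price is power: roughly 57 to 60 % (normal) or 37 to 39 % (t, 4 df) for a 20 % fall in unhealthy grams under the borrowed ICCs, and less for the conjunction than for its weakest part. That is a reason to limit the claim, not to read it from the ratio.

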## Method

### Study design and setting

The design consists of a controlled pre‐post design. The intervention will be organized in three secondary schools in one city in Flanders (Belgium), while three schools from a similar (matched) city (comparable socio‐economical characteristics, population density, size) will be selected as a control setting. The adolescents in the intervention schools will receive a four-week mobile intervention while the control schools will continue their usual practices. The full study period will consist of a baseline test, the four-week ‘The Snack Track School’ intervention (or 4 week control), and a post-test immediately after the intervention.

### Study population and recruitment

The study population will consist of 14- to 16- year-old Flemish adolescents (i.e., 3^rd^- 4^th^ grade of Flemish secondary schools). The necessary sample size for this study was calculated based on the healthy snacking index (i.e., the primary outcome of the intervention study). Assuming an intraclass correlation (ICC) of 0.02 at school level and an ICC of 0.03 at class level with a mean and standard deviation of the healthy snacking index of 37.8 ± 20.2, at least 12 classes with 15 adolescents per school (three intervention schools and three control schools) are needed to detect a difference of 20 % between intervention and control at the 5 % significance level with a power of 80 % [32]. The ICC’s, mean and standard deviation regarding the healthy eating index were based on the earlier cross-sectional REWARD study and the test-retest of the REWARD Food Frequency Questionnaire (FFQ) to measure snack intake ([5], [name] unpublished Data]. To account for possible loss to between pre and post an oversampling of 33 % will be applied. A total sample of 1437 adolescents (control and intervention) in 24 classes per school will be recruited. No exclusion criteria will be applied.

Following the acceptance of the school to participate in the study, parents will receive a letter explaining the purpose of the study and asking for passive consent for participation of their child in the study. In addition, consent of the adolescent will be asked at the beginning of the study.

The study adheres to the Helsinki declaration and the conventions of the council of Europe on human rights and biomedicine. Approval for the intervention study was provided by the Medical Ethics Committee of the University Hospital Ghent and the University of Leuven.

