#### Data management and analysis

After every data collection wave (baseline, post), adolescent questionnaires will be scanned using the scanning software package TELEForm (version 6.1, Cardiff Software Inc., San Marcos, California, USA). Afterwards data will be translated into an SPSS file.

Descriptive analyses will be used at the individual level to compare the intervention and control group at baseline. Linear mixed models taking into account the clusters (child-class-school) will be used to evaluate differences in the primary and secondary outcome variables. In addition, subgroup analyses, and mediating and moderating analyses will be conducted to provide more insight into intervention effects. The process data (including objectively measured data and self-reported data) will be translated in a variable indicating the degree of intervention implementation and will be linked to the effect evaluation.

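### The stated 80 % power ignores that only six schools carry the comparison: with 4 degrees of freedom the plan's own inputs give about 55–57 %

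*Protocol article*

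**What the plan says.** All inputs are in the protocol article, Study population and recruitment. The outcome is the Healthy Snacking Index, with a "mean and standard deviation of the healthy snacking index of 37.8 ± 20.2". For clustering, the calculation starts from "Assuming an intraclass correlation (ICC) of 0.02 at school level"; the corresponding value for classes is "an ICC of 0.03 at class level". The paragraph concludes that "at least 12 classes with 15 adolescents per school (three intervention schools and three control schools) are needed to detect a difference of" a given size. That size is 20 %, the significance level is 5 % and the power is 80 %. An oversampling of 33 % then brings the total to 1437 pupils in 24 classes per school.

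Under Study design and setting, the intervention goes to three schools in one city and the controls are three schools in a matched city. Under Data management and analysis, "Linear mixed models taking into account the clusters (child-class-school) will be used to evaluate differences" for the primary outcome as well as the secondary ones. The power paragraph mentions neither the number of degrees of freedom that six schools provide nor a correlation between baseline and post-test.

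**The concern.** Treatment does not vary within a school. With a non-zero school variance, which the plan itself assumes, the arm effect is judged against variation between schools, and six schools in two arms leave 4 degrees of freedom to estimate that variation. A calculation that uses 1.96 treats the variation as known.

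At stake is the power of the primary hypothesis. A test that respects the six schools keeps the 5 % level but has much less than 80 % power, so a null result would say little about a 20 % difference. A test that reaches the printed power by using a large-sample cut-off exceeds the 5 % level. For the calculation as printed, the two stated properties cannot both hold.

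**Working it through.** **Inputs** (Study population and recruitment): SD 20.2; mean 37.8; school ICC 0.02; class ICC 0.03; 3 schools × 12 classes × 15 pupils = 540 per arm; alpha 0.05. Two readings are needed. The 20 % is taken relative to the mean, 0.20 × 37.8 = 7.56 points, and the test is taken as two-sided. An absolute difference of 20 points would give power near 100 %, so it does not explain the printed 80 %.

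**Standard error of the arm difference**

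Var = 2 × SD² × [school share/3 + class share/36 + pupil share/540]

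The class ICC can be read in two ways:

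- *ICCs add:* 0.02/3 + 0.03/36 + 0.95/540 = 0.00667 + 0.00083 + 0.00176 = 0.00926. SE = √(2 × 20.2² × 0.00926) = 2.749, and 7.56/2.749 = 2.75.
- *Class ICC includes the school ICC:* 0.02/3 + 0.01/36 + 0.97/540 = 0.00667 + 0.00028 + 0.00180 = 0.00874. SE = 2.671, and 7.56/2.671 = 2.83.

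**Reproducing the plan's figure.** With the critical value 1.96, power is 78.5 % (ICCs add) or 80.8 % (inclusive). Under the inclusive reading 11 classes give 79.97 % and 12 give 80.8 %, so 12 is the smallest number that reaches 80 %, as the plan says. Class-level degrees of freedom (about 70) give 77–80 %, so any large-sample reference distribution leads to the same place.

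**Same inputs, six schools.** df = 2 × (3 − 1) = 4, critical t = 2.776, noncentral t with the ratios above:

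| Quantity | ICCs add | Inclusive |
|---|---|---|
| Power, 1.96 cut-off | 78.5 % | 80.8 % |
| Power, t on 4 df | 54.9 % | 57.2 % |
| Difference detectable with 80 % power, 4 df (3.761 × SE) | 10.34 points | 10.05 points |
| The same, as a share of 37.8 | 27.4 % | 26.6 % |
| School share of the variance | 72 % | 76 % |

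A simulation of a t test on school means gave 54.9 % and 57.4 %. Applying 1.96 to a statistic with 4 df has type I error P(|t₄| > 1.96) = 12.2 %.

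**Can more pupils repair it?** All on 4 df:

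- The recruited number with no loss, 1437/6 ≈ 240 per school in 24 classes of about 10: 59–60 %.
- 24 full classes of 15 per school, which is more than planned: 61–62 %.
- Unlimited pupils per school, where only 0.02/3 remains: 68 %.

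The number of schools matters more. With 180 pupils each, four schools per arm (6 df) give 75–78 % and five (8 df) give 87–89 %.

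**The case against.** The strongest reply is that this is a pre-post trial, so the unadjusted post-test comparison understates its power. That stands in part. If baseline cuts the variance by 1 − r² at every level, r = 0.6 gives 73–75 % and r = 0.7 gives 82–84 % on 4 df. But the printed calculation uses no such correlation and the document states none. The gain also depends on where the correlation lies. If baseline explains only variation within schools, r = 0.6 to 0.7 gives 59–61 % (ICCs adding). If adjustment for a school-level baseline costs one of the four degrees of freedom, the optimistic version falls to 64 % and 73 % (same reading). Baseline adjustment may therefore rescue the trial, but it cannot justify the printed figure.

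A second reply is that the paragraph contains no slip of arithmetic, since its inputs do yield its 80 %, and that the degrees-of-freedom method of the mixed model may properly be left to an analysis plan. Both parts are fair. The point here is not that a method goes unnamed, but that the printed power already rests on a reference distribution that six schools do not supply. Nothing in the article commits the final analysis to a 1.96 cut-off, so the 12 % error rate is the price of one way of reaching the stated power, not a planned feature.

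Third, the two-sided test is an interpretation. A one-sided 5 % test on 4 df would still give only 73–75 %.

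**Conclusion.** The concern holds. For the design as printed, 80 % power at the 5 % level is obtained only with a normal or large-df test; with the 4 degrees of freedom that six schools allow, power for a 20 % difference is about 55–57 %, and the difference detectable with 80 % power is about 27 %.

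These figures assume a relative 20 % effect, a two-sided test, equal school sizes, the plan's ICCs and no baseline adjustment. They allow nothing for variation between the two cities. The power of a baseline-adjusted analysis could be close to the unadjusted figure or above 80 %, depending on a correlation that the article does not give. The statement should be corrected, because the primary hypothesis relies on it.

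**What to change.** 1. Restate the sample-size paragraph: with three schools per arm and a test on 4 df, an unadjusted post-test comparison has about 55–57 % power for a 20 % difference, and about 27 % is detectable with 80 % power. Say how the class ICC is defined, that the 20 % is relative to the mean, and whether the test is two-sided.
2. Recompute power for the baseline-adjusted analysis. The pupil-level correlation can come from the sponsor's test-retest data on the questionnaire. Those data may say little about the school-level correlation, so show a range for it, including the case of no school-level gain.
3. State that arm is tested on between-school degrees of freedom and that the school effect stays in the model even when its variance is estimated near zero.
4. If the recomputed power is judged too low, the effective remedy is more schools, not more classes.

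The first three steps take rewording and one recalculation, with no extra pupils. The price is a stated power that will probably be less favourable than 80 %. The fourth step is a design choice and would mean recruiting further schools.
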